### Procedures

Following the current practice within AMPATH, clinical encounter data will be recorded on standard paper encounter forms by medical providers at the point of care, and the existing team of data entry clerks will enter the encounter data into AMRS. Existing data quality personnel will continue to review the data for completeness and consistency and will return problematic forms to cluster administrators for correction. Paper summary sheets with clinical decision-support reminders will be printed for each patient as usual and delivered to facilities without on-demand printing capabilities. In a departure from current practice, additional data clerks will collect data on facility-level treatment compliance, INH stock at AMPATH pharmacies, and IPT eligibility for indeterminate cases in the time window for the 3-month post-initial encounter endpoint.

### Study population

#### Medical facilities

Medical providers with responsibility for diagnosing TB and prescribing TB medication and IPT will be the intervention targets for this study. Due to logistical challenges of provider randomization and concerns about spillover between medical personnel exposed to TB reminders and personnel in the no TB reminders control group, medical facilities rather than individual providers will be randomized to the treatment and control groups.

To be included in the study as a cluster, a facility had to meet the following criteria:
active operations as an HIV Care Clinicuses AMPATH HIV initial and return encounter forms (paper)enters data into AMRS or sends forms to central location for data entryprints or receives printed paper clinical summary sheets with remindersprescribes IPTclassified as a mother facility in the AMPATH network^a^

There are currently 22 AMPATH facilities that meet these criteria. We decided to exclude two facilities to bring the total number of study clusters to 20: a facility that operates as a regional referral hospital and a small facility that is very new to the network.

#### Patients

To be included in the impact analysis, patients must meet the following criteria:
HIV positivecompleted an adult initial encounter at a study cluster during the enrollment period^b^no history of TB or IPTattended at least one additional appointment within 90 days after the initial encounter at any study facility

Patients will not be recruited into the study, per se, as the intervention will be provided to medical personnel and allocated by cluster. Instead, we will run pre-specified data queries in AMRS to identify the cohort of eligible patients.

To be eligible for IPT, and thus eligible for our analysis, patients must have no evidence of active TB. Since HIV-positive adult patients in the AMPATH network typically attend monthly medical appointments, it is reasonable to assume that patients should be classified as eligible for IPT or not eligible for IPT within 2 months of their initial encounter dates. Within 3 months of the initial encounter, patients with no evidence of active TB should have been prescribed INH. Therefore, 3 months after each initial encounter, patients will be classified according to their IPT eligibility and INH prescription status at that time.

Patients who are not eligible for IPT will be excluded from the analysis dataset, while IPT-eligible patients will be included. Importantly, a cluster’s failure to classify a patient as eligible for IPT or not eligible for IPT by the 3-month mark will not exclude the patient from the analysis dataset as improving the screening and diagnostic process is a target of the intervention. Instead, any indeterminate cases at the 3-month post-initial encounter mark will be flagged by our data queries for investigation. We anticipate that the most common reason for indeterminate cases will be missing CXR results. To determine IPT eligibility for study purposes, data clerks will investigate all indeterminate cases and ask medical providers at the cluster to classify the case as eligible for IPT, not eligible for IPT, or still indeterminate. Cases ultimately determined to be eligible for IPT following this review will be included in the analysis dataset; however, these cases will be marked as failures on the primary INH prescription endpoint since, without a determination of eligibility for IPT at the 3-month mark, the patient could not initiate IPT at that time^c^.

The final eligibility criterion is that a patient must attend at least one additional appointment within 90 days of her initial encounter so that her provider has the opportunity to be exposed to the CDSS reminders on the summary sheet. Since a patient’s initial encounter is her first contact with AMPATH at the facility level, there is no summary sheet available during a patient’s initial encounter.

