#### Treatment compliance

All analyses will be on an intention-to-treat basis; thus, we will analyze all observations based on the initial assignment to the study arms, not compliance with the treatment protocol. Yet, treatment compliance will be an important construct to measure in the event of null results so that we can distinguish between intervention and theory failure.

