#### Statistical design considerations

This will be a pragmatic, parallel-group, cluster-randomized superiority trial with a 1:1 allocation to treatment ratio from within four strata. Assuming a desired power of 0.80, alpha of 0.05, 20 clusters equally allocated to treatment and control, 50 patients per cluster, a between-cluster coefficient of variation of 0.25 and a baseline INH prescription rate of 15%, we will be able to detect a minimum shift of almost 8 percentage points in the INH prescription rate, from 15% to almost 23% using a one-tailed test^e^.

Based on a recent retrospective review of AMRS data, we believe that the current rate of INH prescription is between 5% and 25%. Historically, this rate was higher at nearly 40%. No matter where the true baseline rate is in this range, our minimum detectable effect is not projected to rise above 8 percentage points, if everything else is held constant.

The between-cluster coefficient of variation is also important in this calculation. Without cluster-level baseline data on the INH prescription rate, we have to estimate. This variation is often less than 0.25 and rarely exceeds 0.50 [15]. In the previous calculations, we set the between-cluster variation to be 0.25 and scaled it down by 0.75 to account for the benefits of stratification. If the between-cluster variation is really at the high end of this range before scaling (0.50), then the minimum detectable effect climbs to almost 12 percentage points. If we further assume that it is only possible to observe half as many patients per cluster (25), the minimum detectable effect increases to 14 percentage points.

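### The primary denominator depends on an eligibility classification made after exposure to the reminders, so the comparison of prescription rates can be biased in either direction

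*Protocol article*

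**What the plan says.** Under Patients, eligibility is not a baseline property: "3 months after each initial encounter, patients will be classified according to their IPT eligibility and INH prescription status at that time". The consequence is stated directly: "Patients who are not eligible for IPT will be excluded from the analysis dataset, while IPT-eligible patients will be included". The Endpoints section then takes IPT-eligible patients as the denominator of the cluster-level rate.

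The Patients section protects one group. Failure to classify a patient by three months does not by itself remove the patient, and the reason given is that "improving the screening and diagnostic process is a target of the intervention". Data clerks take each indeterminate case to the providers at the cluster, who may answer eligible, not eligible or still indeterminate. A case then called eligible is kept and scored as a failure. Endnote c promises a sensitivity analysis with and without the still-indeterminate cases in the denominator.

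The Objective section names TB case-finding as part of what the reminders should improve, and the Treatment compliance section states: "All analyses will be on an intention-to-treat basis".

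**The concern.** The reminders prompt TB screening. Screening decides who is found ineligible, and that finding decides who is counted. The two arms may then be compared on differently selected patients, even though clusters were randomised. The reason given for keeping unclassified patients applies equally to patients classified as not eligible, yet those are removed and no stated analysis puts them back.

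The review of indeterminate cases adds to this. It rests on providers who know their arm and whose own prescribing is the endpoint. An answer of eligible always adds a failure, while either of the other two answers takes the case out of the primary denominator (endnote c brings the still-indeterminate cases in only as a sensitivity analysis).

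At stake is whether a difference in the primary rate reflects prescribing or a change in who is counted.

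**Working it through.** **1. Reproduce the plan's figure.** The inputs come from Statistical design considerations.

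- Design: "Assuming a desired power of 0.80, alpha of 0.05, 20 clusters equally allocated to treatment and control, 50 patients per cluster". So c = 10 clusters per arm and m = 50.
- Variation and control rate: the section goes on to set "a between-cluster coefficient of variation of 0.25 and a baseline INH prescription rate of 15" per cent.
- Allowance for strata: "we set the between-cluster variation to be 0.25 and scaled it down by 0.75 to account for the benefits of stratification". So k = 0.25 × 0.75 = 0.1875.
- Result and sidedness: "from 15% to almost 23% using a one-tailed test".

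The formula is

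c = 1 + (z_α + z_β)² [p0(1−p0)/m + p1(1−p1)/m + k²(p0² + p1²)] / (p1−p0)².

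Solved for p1 with a one-sided 5% test and 80% power, it gives a detectable difference of 7.72 points, which agrees with the stated figure of almost 8. It also gives 11.59 points with k = 0.375, and 13.93 points with k = 0.375 and m = 25, against the stated almost 12 and 14. Power for 15% v 23% is 82.2%.

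The design standard error with both rates at 15% is √{[2 × 0.15 × 0.85/50 + 0.1875² × 2 × 0.15²]/9} = √(0.00668/9) = 2.72 points.

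**2. Case-finding alone, no change in prescribing.** The protocol gives no TB share and no detection rates, so these are assumptions. Let q be the share with active TB, s the share of those detected and excluded, and r the prescribing rate in undetected cases relative to TB-free patients, who are prescribed at 15% in both arms. Then

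rate = 0.15 [(1−q) + q(1−s)r] / [(1−q) + q(1−s)].

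With r = 0 and detection of 50% in control v 90% in treatment:

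| q | Control | Treatment | Shift (points) |
|---|---|---|---|
| 5% | 0.1425/0.975 = 14.62% | 0.1425/0.955 = 14.92% | +0.3 |
| 10% | 0.135/0.95 = 14.21% | 0.135/0.91 = 14.84% | +0.6 |
| 20% | 0.12/0.90 = 13.33% | 0.12/0.82 = 14.63% | +1.3 |

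The one-sided error is Φ(shift/2.72 − 1.645), which gives 6.2%, 7.7% and 12.1% in place of 5%.

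The sign depends on r. At q = 10% with the same detection rates, r = 1 gives exactly 0 and r = 1.5 gives −0.3. At the extreme of the assumed grid (q = 30%, detection 0% v 100%) the shift runs from +4.5 at r = 0 to −2.25 at r = 1.5.

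**3. Still-indeterminate cases leaving the denominator.** Suppose that a share u of patients, none prescribed, drops out this way, so that rate = 0.15/(1−u). These shares are also assumptions.

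- 10% in control v 5% in treatment: 16.67% v 15.79%, a shift of −0.9 points.
- 20% v 10%: 18.75% v 16.67%, a shift of −2.1 points.

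**4. Both together.** Take q = 10%, detection 50% v 90%, r = 0, and 10% v 5% of TB-free patients still indeterminate. Control is 0.135/(0.81 + 0.05) = 15.70% and treatment is 0.135/(0.855 + 0.01) = 15.61%, a net shift of −0.1 points. With q = 20% and the rest unchanged, the net shift is +0.75.

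**The case against.** The strongest reply has four parts.

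- **Direction.** A reader might infer that better case-finding always raises the treatment-arm rate, so that the bias always favours the intervention. The document does not support this. It requires missed TB cases to stay in the control denominator and to be prescribed INH less often than others. That is plausible: the protocol reports that local practice advises a normal CXR before IPT, fewer than a third of initial encounters in 2013 had a CXR result recorded, and a case indeterminate at three months is a failure by rule. It is not certain. Still-indeterminate cases, which may be more common under control, pull the other way. This part of the reply stands.
- **Size of the contrast.** CXR is usually done at the first visit, before any summary sheet exists. Control clusters keep the existing CXR reminder, and indeterminate cases are reviewed in both arms. All of this may narrow the difference in detection. It limits the size without removing the dependence.
- **Intention-to-treat.** A reader might infer that the statement is simply false. The Treatment compliance section uses the term to mean analysis by assigned arm whatever the compliance, and nothing moves patients between arms. In that sense the plan is consistent, and an effect among IPT-eligible patients is a coherent target. But keeping the assigned arm does not protect a comparison whose members are chosen after exposure.
- **Scope.** Extra sensitivity analyses are often left to an analysis plan that is not shown here. The point, however, concerns an exclusion rule that the article itself fixes, and endnote c shows that the authors dealt with only one of the two groups removed.

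**Conclusion.** The point holds as a risk of bias whose net direction is unknown. The primary analysis set is selected on a classification that follows exposure and that the intervention is meant to change, and nothing stated covers patients found ineligible. Under moderate assumed TB and detection shares, with missed cases never prescribed, the shift is about +0.3 to +1.3 points and the one-sided error about 6% to 12%. Differential loss of still-indeterminate patients can cancel or reverse it. These shifts are small beside the design difference of almost 8 points. They matter mainly if the observed difference is modest.

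**What to change.** Keep the eligible-only analysis and pre-specify beside it the same cluster-level analysis on every patient who meets the criteria that do not depend on the three-month classification: HIV positive, adult initial encounter at a study cluster in the enrolment period, no history of TB or IPT, and a return visit within 90 days. Success is INH prescribed by three months, whatever the later classification. Report eligible, ineligible and still-indeterminate counts by arm, and state in advance that the conclusion will be qualified if the two analyses disagree.

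**Cost.** This is one more run on data already queried. The full-cohort rate is diluted, because patients correctly found to have TB count as not prescribed. With an ineligible share e assumed equal in both arms, m becomes 50/(1−e) and both rates scale by (1−e). Power for the 15% v 23% alternative is then 81.6% (e = 10%), 81.0% (20%) or 80.5% (30%), against 82.2%, a loss of less than 2 points.

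**Limits.** The case-finding shift under this denominator is zero if missed TB cases are not prescribed INH. If they are prescribed as often as others (r = 1, q = 10%, detection 50% v 90%), it is 0.15 × 0.91 − 0.15 × 0.95 = 13.65% − 14.25% = −0.6 points. That is a real difference in prescriptions per patient seen, not selection.

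Nor do the two analyses necessarily bracket the effect. Take 10% TB, the same detection rates, missed cases never prescribed, true rates of 15% v 23%, and 20% v 5% of the cohort still indeterminate and unprescribed. Eligible-only then gives 13.5/75 = 18.0% v 20.7/86 = 24.1% (6.1 points), and the full cohort gives 20.7% − 13.5% = 7.2 points. Both fall below the true 8. The counts by arm are therefore needed to interpret either result.

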### Ethical considerations

This protocol has been reviewed and approved by the Moi University School of Medicine/Moi Teaching and Referral Hospital Institutional Research and Ethics Committee (0001055), the Indiana University Institutional Review Board (1307011750), and the Lifespan Research Protection Office (0000396, 00004624). The approving ethics committees did not require individual patient consent given the nature of the intervention.

### Statistical analysis

#### Study objectives as statistical hypotheses

##### Primary hypothesis

*H*_0_ There will be no measurable difference in the rate of INH prescriptions among IPT-eligible patients (i.e., patients with no evidence of active TB) who receive care from treatment or control clusters.

*H*_*a*_ The INH prescription rate among IPT-eligible patients receiving care from medical providers at treatment clusters will be greater than the INH prescription rate among IPT-eligible patients receiving care from medical providers at control clusters.

##### Secondary hypothesis

*H*_0_ There will be no measurable difference in the time lapse from initial encounter to INH prescription among IPT-eligible patients (i.e., patients with no evidence of active TB) who receive care from treatment or control clusters.

*H*_*a*_ The time lapse from initial encounter to INH prescription among IPT-eligible patients receiving care from medical providers at treatment clusters will be shorter than the time lapse from initial encounter to INH prescription among IPT-eligible patients receiving care from medical providers at control clusters.

#### Endpoints

INH will be considered prescribed when there is an entry in AMRS indicating that a medical provider prescribed INH ^d^. The denominator for the calculation of the cluster-level prescription rate will be the number of IPT-eligible patients in the study who completed an initial and return encounter during the study period. The time lapse from the date of a patient’s initial encounter to the date of INH prescription will be calculated in days. The endpoint for the INH prescription time lapse will be calculated by averaging cluster-level INH prescription lapse means among IPT-eligible patients across the treatment and control groups separately.

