**Methods/Design:**

This study will examine the use of clinical decision-support reminders to improve rates of initiation of preventative treatment in a TB/HIV co-morbid population living in a TB endemic area. This will be a pragmatic, parallel-group, cluster-randomized superiority trial with a 1:1 allocation to treatment ratio. For the trial, 20 public medical facilities that use clinical summary sheets generated from an electronic medical records system will participate as clusters. All HIV-positive adult patients who complete an initial encounter at a study cluster and at least one return encounter during the study period will be included in the study cohort. The primary endpoint will be IPT prescription at 3 months post the initial encounter. We will conduct both individual-level and cluster-level analyses. Due to the nature of the intervention, the trial will not be blinded. This study will contribute to the growing evidence base for the use of electronic health interventions in low-resource settings to promote high-quality clinical care, health system optimization and positive patient outcomes.

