##### Individual-level regression analysis

In addition to the analyses based on cluster-level summaries, we will also use regression models with individual-level data that account for between-cluster variation. Specifically, we will evaluate the reliability of logistic regression random effects models and generalized estimating-equation approaches to model our binary outcome. We will use Cox regression with random effects to model the time to INH prescription. Individual-level covariates will be limited to data collected reliably in AMRS, such as age, gender and CD4 count.

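### The secondary time-lapse endpoint averages days that only prescribed patients have, so it conditions on the primary outcome and does not match the planned time-to-event analyses

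*Protocol article*

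**What the plan says.** The Endpoints section sets the patient-level quantity: "The time lapse from the date of a patient’s initial encounter to the date of INH prescription will be calculated in days". It then gives the endpoint as "calculated by averaging cluster-level INH prescription lapse means among IPT-eligible patients across the treatment and control groups separately". It names no value, time horizon or censoring rule for an eligible patient who is never prescribed.

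The Secondary hypothesis section is about IPT-eligible patients as a whole: the lapse in the reminder arm "will be shorter than the time lapse from initial encounter to INH prescription among IPT-eligible patients receiving care from medical providers at control clusters".

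The analysis sections treat the same question as time-to-event. Cluster-level summaries plans Kaplan-Meier estimates over 3 months and a log rank test. Individual-level regression analysis adds: "We will use Cox regression with random effects to model the time to INH prescription".

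Two other statements matter here. The abstract fixes the primary outcome: "The primary endpoint will be IPT prescription at 3 months post the initial encounter". The Patients section explains that "there is no summary sheet available during a" patient's first visit, so a reminder can first act at a return visit.

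**The concern.** A patient without a prescription has no prescription date, so a mean of days to that date can be taken only over prescribed patients. Being prescribed is the primary outcome and is what the reminders are meant to change. The two groups averaged are therefore selected after randomisation by a process the intervention influences, and a difference between them need not reflect faster prescribing.

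The mean also drops patients whom the protocol deliberately keeps elsewhere. Under Patients, cases judged eligible only on later review stay in the analysis as primary-endpoint failures, because better screening is a target of the intervention. Those without a prescription contribute nothing to the lapse mean.

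Time to IPT initiation is one of the two parts of the main research question in the Objective section. A reported mean lapse that disagrees with the log rank and Cox results, or with a successful primary result, would leave the reader unsure which one answers it.

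**Working it through.** **Inputs from the protocol.** Statistical design considerations gives the planning rates, "from 15% to almost 23% using a one-tailed test", with 20 clusters equally allocated, 50 patients per cluster, and a between-cluster coefficient of variation of 0.25 scaled by 0.75, so k = 0.1875. It puts the current rate between 5% and 25%. Visits are typically monthly (Patients).

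**Assumptions.** The planning rates are read as 3-month rates, 3 months is taken as 90 days, and 23% stands for almost 23%. The protocol says nothing about when prescriptions occur, so every timing pattern below is assumed.

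**The plan's own figure.** The protocol gives no power figure for the time-lapse endpoint. The rates come from the primary-endpoint calculation, which reproduces with c = 1 + (z_α + z_β)²[p0(1−p0)/m + p1(1−p1)/m + k²(p0² + p1²)]/(p1−p0)². With c = 10, m = 50, one-sided alpha 0.05 and power 0.80, the detectable shift from 15% is 7.72 points, which matches the stated value of almost 8. This only confirms the rates used below.

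**Who contributes to the mean.** Without a prescription: 1 − 0.15 = 85% of control and 1 − 0.23 = 77% of treatment patients. Over the 5% to 25% baseline range the unprescribed share is 95% to 75%. A cluster of 50 supplies about 50 × 0.15 = 7.5 lapses in control and 50 × 0.23 = 11.5 in treatment.

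**Two measures compared.** Mean among prescribed = Σ(share × day)/Σ share. Mean over all eligible patients to day 90 = Σ(share × day) + (1 − Σ share) × 90. All clusters in an arm are given the same rate and timing, so the average of cluster means equals the arm mean.

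*Pattern 1: control 15% at day 30; treatment the same 15% plus 8% at day 60.*
- Among prescribed: control 30.0; treatment (15×30 + 8×60)/23 = 40.4. Treatment looks 10.4 days slower.
- All eligible: control 0.15×30 + 0.85×90 = 81.0; treatment 0.15×30 + 0.08×60 + 0.77×90 = 78.6. Treatment is 2.4 days faster.

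*Pattern 2: the added 8% also at day 30.*
- Among prescribed: 30.0 v 30.0, no difference.
- All eligible: 81.0 v 0.23×30 + 0.77×90 = 76.2.

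*Pattern 3: control 15% at day 60; treatment the same plus 8% at day 30.*
- Among prescribed: 60.0 v (15×60 + 8×30)/23 = 49.6, the correct direction.
- All eligible: 0.15×60 + 0.85×90 = 85.5 v 0.15×60 + 0.08×30 + 0.77×90 = 80.7.

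**A wider set.** Five further patterns spread 15% (control) and 23% (treatment) over days 0/30/60/90. In each, cumulative prescription in treatment is at or above control at every visit. Differences are treatment minus control, in days.

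| Percent prescribed at days 0/30/60/90: control; treatment | Among prescribed, C v T | Difference | All eligible, C v T | Difference |
|---|---|---|---|---|
| 3/5/4/3; 3/8/7/5 | 44.0 v 48.3 | +4.3 | 83.1 v 80.4 | −2.7 |
| 3/6/4/2; 3/6/8/6 | 40.0 v 52.2 | +12.2 | 82.5 v 81.3 | −1.2 |
| 7.5/3.5/2.5/1.5; 7.5/6.5/5.5/3.5 | 26.0 v 36.5 | +10.5 | 80.4 v 77.7 | −2.7 |
| 0/5/5/5; 0/7.67/7.67/7.66 | 60.0 v 60.0 | 0.0 | 85.5 v 83.1 | −2.4 |
| 0/5/5/5; 0/11/7/5 | 60.0 v 52.2 | −7.8 | 85.5 v 81.3 | −4.2 |

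**With sampling variation.** The five patterns were simulated with 10 clusters per arm, 50 patients each, k = 0.1875 and 1,500 runs. In table order, the mean among prescribed was longer in treatment in 82%, 99%, 98%, 51% and 3% of runs. The 51% is a coin toss, because the true difference there is zero. The all-eligible mean pointed the wrong way in 4%, 21%, 7%, 1% and 0% of runs.

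**The case against.** The strongest defence is that no test is attached to the averaged lapse. The tests named for time to prescription are the log rank test and the random-effects Cox model, and both keep unprescribed patients at risk. A reader might infer that the secondary hypothesis will be tested on a biased comparison, but the protocol does not support that. This defence stands, and it confines the defect to the defined endpoint, the figure reported for it, and its mismatch with the planned analyses.

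A reader might also infer that, with no summary sheet at the first visit, added prescriptions must come late and the treatment mean must rise. That does not follow. The sign depends on when added prescriptions fall relative to those in control, and the protocol gives no such data. The first-visit argument needs an appreciable share of prescribing on day 0. The protocol gives some reason to expect little of that: a normal chest radiograph is advised before IPT, and eligibility is expected to be settled within 2 months. Pattern 1 has no day-0 prescriptions; its reversal comes entirely from placing the added 8% at day 60.

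Finally, the endpoint sentence refers to IPT-eligible patients, not to prescribed patients, and an article may leave the handling of unprescribed patients to the analysis plan. This stands in part. The wider group may have been intended, but the article does fix a formula, a mean of days to a prescription date, and nothing stated makes it computable for patients without one.

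**Conclusion.** The point holds as a defect in the definition of a secondary endpoint, and it should be fixed. As written, the endpoint rests on about 15% of control and 23% of treatment patients, selected by the primary outcome. It is not the quantity that the secondary hypothesis or the planned survival analyses address.

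The supported claim about direction is that the endpoint can mislead, not that it will. Across the five spread patterns the difference in mean lapse ran from −7.8 to +12.2 days, while the all-eligible difference was always in favour of treatment, by 1.2 to 4.2 days. Those sizes rest on the planning rates, a 90-day horizon and assumed timings. The conditioning itself rests only on the stated definition. The primary endpoint is untouched, and so are the log rank and Cox analyses as far as this problem goes.

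**What to change.** In the Endpoints section, define the secondary endpoint as time from initial encounter to INH prescription in all IPT-eligible patients, with those not prescribed censored at 3 months (90 days). Test it by the methods already planned: Kaplan-Meier with the log rank test, and Cox regression with random effects. Summarise it per cluster by Kaplan-Meier cumulative prescription or by restricted mean days to day 90, and average the cluster values by arm. If mean days among prescribed patients is still reported, label it descriptive and show the number of patients behind it.

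The change uses the same AMRS dates and needs no new data. Because the intervention launched on 11 April 2014 (Trial status), it is a post-launch change to a secondary endpoint definition and should be documented as one, with its date and reason.
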